## Abstract

**Introduction:**

Adaptive deep brain stimulation (aDBS), based on the detection of increased beta oscillations in the subthalamic nucleus (STN), has been assessed in patients with Parkinson’s disease (PD) during the immediate postoperative setting. In these studies, aDBS was shown to be at least as effective as conventional DBS (cDBS), while stimulation time and side effects were reduced. However, the effect of aDBS on motor symptoms and stimulation-induced side effects during the chronically implanted phase (after the stun effect of DBS placement has disappeared) has not yet been determined.

**Methods and analysis:**

This protocol describes a single-centre clinical study in which aDBS will be tested in 12 patients with PD undergoing battery replacement, with electrodes implanted in the STN, and as a proof of concept in the internal globus pallidus. Patients included will be allocated in a pseudo-randomised fashion to a three-condition (no stimulation/cDBS/ aDBS), cross-over design. A battery of tests will be conducted and recorded during each condition, which aim to measure the severity of motor symptoms and side effects. These tests include a tablet-based tapping test, a subscale of the Movement Disorder Society-unified Parkinson’s disease rating scale (subMDS-UPDRS), the Speech Intelligibility Test (SIT) and a tablet-based version of the Stroop test. SubMDS-UPDRS and SIT recordings will be blindly assessed by independent raters. Data will be analysed using a linear mixed-effects model.

**Ethics and dissemination:**

This protocol was approved by the Ethical Committee of the University Medical Centre Groningen, where the study will be carried out. Data management and compliance to research policies and standards of our centre, including data privacy, storage and veracity, will be controlled by an independent monitor. All the scientific findings derived from this protocol are aimed to be made public through publication of articles in international journals.

**Trial registration number:**

NTR 5456; Pre-results.

Strengths and limitations of this studyThis protocol aims to assess both efficacy and side-effect profile of adaptive deep brain stimulation.The stun effect will not present in the patient population to be included in this protocol.Intraoperative testing will minimise exposure time for electrodes and risk of infection.Testing and washout periods will be limited by the intraoperative time available.The intraoperative setting will limit the tests available to be assessed in patients with Parkinson’s disease.

## Introduction

### Background and rationale

Deep brain stimulation (DBS) is currently one of the most effective advanced treatments for patients with Parkinson’s disease (PD). At present, conventional DBS (cDBS) provides the continuous delivery of fixed-frequency and fixed-amplitude electrical pulses through the electrodes implanted mostly in either the subthalamic nucleus (STN) or the internal globus pallidus (GPi).^1 2^ Although cDBS is an effective treatment, it still has limitations in terms of efficacy, side effects and efficiency, and these have not undergone substantial improvements since the implementation of cDBS in clinical practice, approximately 20 years ago.^3^ However, new DBS systems directed to improve current stimulation algorithms are currently under development. These systems are often referred to as adaptive DBS (aDBS), as they aim to modulate the delivery of electrical stimulation, controlled by the detection of symptoms, such as tremor, or aberrant signals (biomarkers) that have been implicated in the pathophysiology of the disease.^4^ The ultimate goal of aDBS systems is to reduce the total amount of stimulation delivered, in a way in which beneficial effects of DBS are enhanced, while side effects are reduced.^5^ Furthermore, decreasing the total amount of stimulation delivered will allow to extend the battery life(span) of DBS devices.

Several biomarkers in PD have been proposed for use as a feedback signal for aDBS.^6^ Currently, the presence of prominent beta oscillations (13–35 Hz), in either the STN or the GPi, seems to be the most promising since it correlates with the severity of bradykinesia and rigidity.^7^ Evidence to date suggests that aDBS may be at least as effective as cDBS systems, while stimulation time and side effects are reduced.^8–10^ However, virtually all aDBS experiments based on beta oscillations have thus far only been tested in the immediate postoperative setting. Although aDBS has been evaluated mostly with regard to the STN, preliminary evidence indicates that aDBS could be equally effective when applied to the GPi.^11^ The correlation of other prominent PD symptoms (such as tremor) with beta oscillations is far less robust. Therefore, the impact of aDBS on these symptoms is yet to be addressed.^12 13^

Besides its effect on motor symptoms, a common side effect that could potentially be addressed by aDBS is stimulation-induced dysarthria. Preliminary data in the immediate postoperative phase showed that aDBS did not induce dysarthria, in contrast to cDBS.^14^ Likewise, due to the reduction in the total amount of stimulation that occurs in aDBS, this new technology could potentially help to tackle DBS-related side effects in executive functions, such as impaired response inhibition.^15 16^ Patients with PD treated with DBS are prone to make more mistakes in inhibitory control tests (eg, the Stroop task).^17^ Response inhibition is a fundamental cognitive function, and its impairment could lead to impulsive conduct.^18^ For that reason, it is possible that stimulation-related impulsivity is the result of an impairment of response inhibition caused by DBS.^19 20^ It was first proposed that this side effect was due to unintended stimulation of limbic areas of the STN.^21^ However, it has been shown recently that DBS has a positive effect on risk-reward decision behaviour in patients with PD, and that such an effect was mostly dependent on stimulation of the motor part of the STN.^22^ This finding indicates that at least some of the non-motor effects of DBS are mediated through direct stimulation of the motor part of the STN. This is supported by increasing evidence that indicates that the motor and non-motor functions of the STN are not perfectly segregated.^23^ It has been shown that beta oscillations in the motor STN play a significant role in adequate response inhibition.^24^ For that reason, stimulation-induced impulsivity could be the result of an excessive beta suppression produced by continuous stimulation. Therefore, aDBS might be used as an additional option to address stimulation-induced impulsivity, since aDBS has the potential to provide a functional selectivity, by only triggering stimulation based on (primarily) motor biomarkers (eg, beta oscillations), only when a threshold is exceeded. As a result, only excessive beta activity would be suppressed.

### Objectives

The aim of this study is to assess whether aDBS provides a similar motor improvement compared with cDBS, while limiting the presence of stimulation-induced side effects in patients with chronically implanted electrodes. Stimulation efficacy is assessed using a battery of tests aiming to measure the motor response to different conditions and the severity of dysarthria and/or impulsivity. The goals of this protocol are summarised in three questions:Is aDBS at least as efficacious as cDBS in terms of motor improvement?Is the speech-related and response inhibition side-effect profile of aDBS lower than that of cDBS?What is the amount of stimulation provided in aDBS compared with cDBS?

### Trial design

This protocol describes an exploratory study in which patients with PD with DBS electrodes implanted in the STN are allocated to a three-condition (no stimulation (NoStim)/cDBS/aDBS), cross-over design (figure 1). The conditions are pseudo-randomised in a 2:1:1 format, in such a way that for every two patients who start with no-stimulation, one patient will receive aDBS first and one will have cDBS first. The main reason for this proposed pseudo-randomisation is to minimise the impact that an incomplete washout effect derived from stimulation could have on the scores of NoStim condition, as this condition is the baseline for the comparison of the effect of the two stimulation modalities. In four patients, stimulation conditions will be separated by a NoStim condition to minimise the carryover effect that cDBS could have on aDBS (or vice versa). Lastly, NoStim will be the last condition in two patients in order to partially balance the effects of training or fatigue on the tasks. Additionally, pilot data could be collected from two patients in order to explore the effects of aDBS on the GPi.

**Figure 1 F1:**
[figure not shown]
Trial design and pseudo-randomisation block. aDBS, adaptive deep brain stimulation; cDBS, conventional DBS; GPi, internal globus pallidus; PD, Parkinson’s disease; subMDS-UPDRS, subscale of the Movement Disorder Society-unified Parkinson’s disease rating scale; SIT, Speech Intelligibility Test.

The performance of several tasks during the three conditions will take place during the battery replacement surgery, when a temporal externalisation of the DBS extension wires is performed. This means that subjects to be included have had their DBS electrodes implanted for at least 3–5 years, and therefore the stun effect is not present in this patient population. It was decided to perform this protocol intraoperatively as it allows the surgery to be completed in one session, minimising the time that electrodes are externalised and patients are exposed to potential risks of infection.

## Methods and analysis

### Methods: participants, interventions and outcomes

#### Study setting

This is a single-centre study at the University Medical Centre Groningen.

### Inclusion criteria

Patients with PD with DBS electrodes implanted bilaterally in the STN. A maximum of two patients with PD with electrodes implanted in the GPi would be allowed as pilot data.Patients are cognitively capable of performing the tests included in this protocol. This item is subjectively evaluated during the patient interview, by looking at the performance of the candidate when completing a trial set of the tablet-based tests used during the experiment.Able to provide written informed consent.Physical condition that enables 20–30 min of testing. This is evaluated according to the clinical records and the fragility of the patient (determined by the treating neurologist).Ability to undergo testing in the OFF dopaminergic state, determined by the clinical condition of the patient after medication withdrawal.

### Exclusion criteria

Patients who cannot tolerate battery replacement under local anaesthesia (eg, presence of severe OFF medication tremor, severe anxiety, etc).<18 years old.Clinical disorders or diseases that could interfere with clinical assessment (eg, vision impairment that cannot be corrected with glasses, severe limb movement restriction).Cognitive impairment sufficient to prevent the patient to consider and retain the necessary information to make a decision regarding the participation in the study.

### Investigational device

The responsive (closed loop) aDBS is delivered through a custom-made stimulation-amplifier which allows local field potentials (LFPs) to be recorded during the application of DBS. With this device, LFPs are filtered in real time around a subject’s specific beta frequency (±3 Hz around peak).^9^ Afterwards, a median threshold is selected in order to deliver monopolar stimulation every time that beta activity in the rectified filtered LFP exceeds the predefined threshold. Stimulation pulses are charge-balanced and asymmetric, mirroring the waveform of the standard clinical Medtronic Activa PC. Pulses are delivered at 130 Hz with a pulse width of 60 µs (standard clinical parameters) using a ramping period of 250 ms at onset and offset in order to help limit the presence of paraesthesias, autonomic or other non-specific side effects, such as dizziness or nausea.^25^ From the four contacts available for each electrode lead, two electrodes are required to perform bipolar LFP recordings (either contacts 0–2 or 1–3), while one electrode (in between the two recording electrodes) is left available for stimulation (either contact 1 or 2). The stimulation-amplifier has been built to strict safety guidelines (Report 90 BS EN60601-1 safe design, construction of medical equipment) and extensively tested,^8 9 11 26^ and found to be safe and reliable.

### Procedure

Patients have to skip at least one medication dose and are not allowed to be under the effect of prolonged-release dopaminergic medication in order to be classified as OFF medication before surgery. Patients are brought to the operating theatre for their battery replacement procedure. After the battery is exposed, the old battery is detached from the DBS electrodes and explanted. At this moment, two temporary wires are attached to the DBS electrode extension cables and connected to a combined stimulator and amplifier (see previous section). A brief rest recording of 30–60 s is performed from each of the two bipolar montages (0–2 or 1–3) available for each hemisphere. Power spectral density estimates are obtained from each rest recording, and the bipolar contact pair (0–2 or 1–3) per hemisphere with the highest beta peak power is selected. Monopolar cDBS is then titrated using the available contact located between the selected recording contacts. The voltage for monopolar stimulation is titrated initially based on an approximation of the voltage used in clinical practice for each individual patient (independently of the montage used in clinical practice). Voltage is increased or decreased according to the presence of side effects, clinical effect and interference with LFP recordings (in practice, we have seen that voltages>3.5 V are more prone to cause interference with the recordings, and these are also rare stimulation parameters in clinical practice). Once an optimum stimulation voltage is established, the patients are assigned to each of three counterbalanced conditions in which the patient is either stimulated with aDBS or cDBS, or not stimulated, separated by washout periods of 1–3 min, according to the remaining time available. Stimulation parameters (voltage, frequency, pulse width and contact selection) remain constant for both aDBS and cDBS, differing only in the timing of stimulation delivered according to beta detection. As battery replacements are performed under local anaesthesia, we aim to limit the duration of the experiment to a maximum of 25–30 min.

### Clinical tests and outcomes

Each patient performs the following tasks in each of the three pseudo-randomised conditions:Tablet-based tapping test: several analogue and digital versions of the tapping test have been validated to objectively measure the presence of bradykinesia in patients with PD.^27–29^ We developed a custom tablet-based finger tapping test using the PsyPad platform.^30^ In this test, a tablet is presented to the patient, in which two squares appear at the left and right sides of the screen (figure 2). The patient then has to press the squares in an alternating pattern. We tested this set-up, as a proof of principle, on a patient with PD who underwent battery replacement,^26^ using 50 tapping iterations per condition. In order to optimise the time available for the battery of tests, it was decided to reduce the iterations to 20. Since the duration of each iteration was approximately 500 ms, 20 iterations (10 back-and-forth screen tapings) will be roughly equivalent to 10 finger tapings, which is the amount of taps required to measure tapping items from the Movement Disorder Society-unified Parkinson’s disease rating scale (MDS-UPDRS).Subscale of the MDS-UPDRS (subMDS-UPDRS)^31^ (Part III, items 3.4, 3.5, 3.6, 3.15, 3.17 a, b): as patients are lying on the operating table during the experiment, only selected items can be performed by the patients. The items that are included and filmed are finger tapping, hand movements, pronation-supination, rest tremor and postural tremor.Speech Intelligibility Test (SIT): this is a modified version of the Assessment of Intelligibility for the Dysarthric Speech.^32 33^ In this test, the patient is instructed to read out a list of 18 sentences (approximately 110 words per condition), while the speech is recorded with a mobile application. The words that form each sentence are randomly chosen, taking into account that each sentence must follow the correct order of a proper grammatical construction. Voice recordings are sent to a speech therapist, who blindly evaluates the sentences and writes them down. Afterwards, the sentences written by the speech therapist are compared with the original list, and the amount of words that coincide are expressed as a percentage of the total words.Tablet-based version of the Stroop test^34^: in this test, 20 colour words are presented to each patient in a sequential order, and each word is coloured as shown in figure 3. From those 20 words, five are coloured in the same colour as the word written (congruent), while 15 words are coloured in a colour different from the word written (incongruent). We chose an unbalanced design as our main focus is the effect of stimulation on incongruent words between conditions, rather than the effect of stimulation between congruent and incongruent words. For each word presented, four buttons are presented at the bottom of the tablet screen, each containing different colour words. The patient has to select the button containing the colour word presented on the screen, independently of the colour in which the word is coloured in. Reaction times and accuracy for each trial are directly uploaded to an online database, from which they can be extracted for data analysis.

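### As written, the Stroop rule asks patients to match the written word and ignore its colour, which suits the response-inhibition question poorly; reaction time on incongruent words would also mix in motor speed

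*Protocol article*

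**What the plan says.** All references are to the protocol article.

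- **Response rule** (Clinical tests and outcomes): the stated instruction is this: "select the button containing the colour word presented on the screen, independently of the colour in which the word is coloured in". For the response, "four buttons are presented at the bottom of the tablet screen, each containing different colour words".
- **Trial mix** (same section): of 20 words per condition, "five are coloured in the same colour as the word written (congruent), while 15 words are coloured in a colour different" from the written word. The uneven split is justified because "our main focus is the effect of stimulation on incongruent words between conditions, rather than the effect of stimulation between congruent and incongruent words".
- **Data captured** (same section): "Reaction times and accuracy for each trial are directly uploaded to an online database".
- **Purpose** (Background and rationale): "Patients with PD treated with DBS are prone to make more mistakes in inhibitory control tests (eg, the Stroop task"; the text goes on to link impaired response inhibition to impulsivity.
- **Study question** (Objectives, second question): "Is the speech-related and response inhibition side-effect profile of aDBS lower than that of cDBS".
- **Analysis** (Statistical methods): simple scores from all four tests are compared between aDBS and cDBS or no stimulation in a linear mixed-effects model. The section does not say which Stroop score is used.

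**The concern.** A Stroop task tests inhibition when the patient must suppress reading in order to report the colour. Under the rule as printed, the target is the written word and the answer is that same word on a button. Reading leads straight to the correct answer, and the colour is only a distractor. The test would then put little demand on the function it was chosen to measure.

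The Stroop test is the only response-inhibition measure in the battery; the other three cover tapping, motor signs and speech. If it makes little inhibitory demand, finding no difference between aDBS and cDBS would be uninformative on half of the second study question, yet could be reported as a favourable side-effect profile. An analysis plan cannot repair data collected under the wrong target.

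A second, separate issue concerns reaction time. Responses are touches on a tablet by patients who are OFF medication, under conditions chosen because they alter hand speed. A comparison of incongruent reaction times between conditions cannot tell faster hands from better inhibition.

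**Working it through.** **1. Rule against purpose.** No figure in the protocol depends on this point, so there is none to reproduce. The check sets the sections side by side.

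| Element | Clinical tests and outcomes | Needed for the aim in Background and Objectives |
|---|---|---|
| Target | Written word | Colour shown |
| To be ignored | Colour shown | Written word |
| Habitual response (reading) | Correct | Wrong on incongruent trials |

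The first column follows from the text. That reading is the habitual response is general knowledge of the task, not a statement in the protocol. The mismatch affects accuracy as well as reaction time, because a patient who simply reads scores correctly on every trial.

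**2. Reaction time on incongruent words.** Write a between-condition difference as a motor shift m, common to both trial types, plus an inhibition shift h, present on incongruent trials only. Then:

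- incongruent-only difference = m + h
- difference in (incongruent minus congruent) = (m + h) − m = h

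The protocol gives no values for m or h. The values below are assumed for illustration (negative means faster).

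| m (ms) | h (ms) | Incongruent only (ms) | Incongruent minus congruent (ms) |
|---|---|---|---|
| −100 | 0 | −100 | 0 |
| −100 | +50 | −50 | +50 |
| −100 | +100 | 0 | +100 |
| 0 | +50 | +50 | +50 |

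In row 1 a pure motor gain looks like better inhibition. In row 3 a real inhibitory cost is hidden. In row 4, with no motor shift, the two measures agree.

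**3. Precision of the contrast.** Inputs from the protocol: 15 incongruent and 5 congruent trials per condition. Let s be the trial standard deviation, assumed equal for both types, with independent trials.

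- SE of the incongruent mean, one condition: s√(1/15) = 0.258s
- SE of incongruent minus congruent, one condition: s√(1/15 + 1/5) = 0.516s
- Difference between two conditions: s√(2/15) = 0.365s and s√(2(1/15 + 1/5)) = 0.730s

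The contrast can be computed from the planned data, at twice the trial-level standard error of the incongruent mean (0.516/0.258 = 2.0).

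**The case against.** **The sentence may be a slip.** The figure showing the two trial types is not available here, and the app may already score the displayed colour. This stands. It limits the finding to the task as described, but either the task or the text still needs correcting.

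**The plan does not say that only incongruent reaction time is analysed.** A reader might infer this from the stated focus, but the documents do not support it. The text speaks of a main focus, congruent trials are collected, accuracy is recorded for every trial, and Statistical methods names only simple scores. Background describes the deficit as mistakes, which points to accuracy. The choice of Stroop score may also sit in an analysis plan that is not shown. The reaction-time point is therefore conditional: it applies if reaction time is compared on the stated focus.

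**The motor confounding is weak where it matters most.** The second question compares aDBS with cDBS, and the study expects similar motor benefit from both. The confounding is then largest against no stimulation and small for aDBS versus cDBS. This also stands, but similar motor effect is what the trial sets out to test, so it cannot be taken as given.

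**The study is exploratory.** Its sample size rests on the motor scale, and under Order of the tests the Stroop test comes last and may be omitted when time is short. This tempers the consequences for the trial as a whole. It does not make the rule fit its purpose.

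**Conclusion.** The concern holds in a limited form. The printed response rule is word matching and is poorly suited to the response-inhibition question, which rests on this test alone. If followed exactly, it undercuts half of the second objective; the speech half is untouched. In addition, any reaction-time comparison on the stated focus would mix motor speed with inhibition by the full size of the motor shift.

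Three stronger readings are not supported:

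- **That the test cannot measure inhibition at all.** A mismatching colour is still a distractor, though a weak one for this purpose.
- **That interference will be close to zero and accuracy close to ceiling.** The protocol gives no data from which to derive either.
- **That the 15:5 split is an error and should be 10:10.** Equal numbers would lower the standard error of the contrast from 0.516s to √(1/10 + 1/10)s = 0.447s, about 13%. They would also raise that of the incongruent mean from 0.258s to √(1/10)s = 0.316s, about 22%. The protocol gives a reason for its split, so this is a trade-off.

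The conclusion assumes that reading is the habitual response. The reaction-time part also assumes that motor slowing is roughly additive across trial types.

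**What to change.** 1. Check the programmed task. If the written word is the target, change the instruction and scoring so that the correct button names the colour in which the word is shown. If the app already works that way, correct the sentence under Clinical tests and outcomes.
2. Name accuracy on incongruent trials as the error measure, in line with the emphasis on mistakes in Background and rationale.
3. If reaction time is analysed, use the condition by congruency contrast. State that it assumes roughly additive motor slowing and that five congruent trials per condition limit its precision.

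The cost is a change of instruction or scoring, or one corrected sentence, plus one model term. The number of trials and the theatre time stay as they are. Protocol amendments shows that patients had already been measured before this version. If the programmed rule does change, results obtained under the two rules should be kept apart and reported as such.
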